# Investigating the effects of a daily multidisciplinary intensive outpatient rehabilitation program on innovative biomarkers in people with Parkinson’s disease: Study protocol for a phase III randomized controlled clinical trial

**DOI:** 10.1371/journal.pone.0309405

**Published:** 2024-10-23

## Abstract

**Background:**

To date, there has been no medication that has prevented the progression of Parkinson’s disease (PD). Many benefits of intensive and multidisciplinary rehabilitation program for PD are supported by clinical, epidemiological, and experimental data. The main question is whether high-intensity motor and cognitive exercises have an effect on the disease’s biological mechanisms.

**Objective:**

This study protocol is a Randomized Controlled Trial (RCT) designed to determine the efficacy of an experimental, intensive, and multidisciplinary treatment in comparison to a home-based self-treatment in improving biomolecular and functional parameters in PD.

**Methods:**

A total of 72 participants will be randomly allocated to two different groups, experimental (n = 36) and control group (n = 36). The rehabilitation program will last 6 consecutive weeks and will involve the execution of a total of 30 sessions, one for each day of the week from Monday to Friday. Participants allocated to the control group will carry out a home-based self-treatment program that includes muscle-stretching and active mobilization exercises for 40’/day for 6 consecutive weeks. The primary outcome measure is the effects of both treatments on a new set of molecular biomarkers such as oligomeric alpha-synuclein and neurotrophic factors measured in peripheral neural derived extracellular vesicles (NDEVs). Secondary outcomes will include changes of motor and non-motor symptoms, balance and gait performance and cognitive functioning. This RCT has been registered as “Intensive Multidisciplinary Rehabilitation and Biomarkers in Parkinson’s Disease” on 30 May, 2022 to ClinicalTrials.gov with the Study ID number: NCT05452655.

**Discussion:**

This rehabilitation program is believed to be crucial in modifying biomolecular and functional parameters in people with PD. We expect that this study will provide additional evidence to understand the impact of an aerobic and intensive rehabilitation program on brain plasticity in patients with PD.

## Introduction

Parkinson’s Disease (PD) is a chronic and slowly progressive neurodegenerative disease, and its prevalence is on the rise at a faster pace compared to other neurological disorders [1]. PD is characterized by a wide range of both motor and nonmotor symptoms (NMS).

Rigidity, bradykinesia, resting tremor are common motor symptoms in PD arising in the early stages of the disease and are mostly influenced by the degeneration of dopaminergic neurons in substantia nigra pars compacta [2]. PD symptoms are now acknowledged to be more heterogeneous. Motor and non-motor features like cognitive impairment, sleep disorders, autonomic dysfunction, pain, fatigue, psychiatric symptoms, and olfactory dysfunction contribute to worsening the disability [3, 4] and the quality of life [5, 6].

In the literature, consistent evidence supports the use of levodopa and dopamine agonists as the principal treatment for motor symptoms [7]. However, despite pharmacological treatment, a majority of people with PD (PwPD) keep experiencing a broad spectrum of motor and nonmotor symptoms [8, 9]. In this context, several other therapies have been shown effective on other symptoms, even though evidence is less conclusive for PD treatments both in the early and advanced stages of the disease [10]. In light of this, an expanding body of research is documenting non-pharmacological treatments for PD symptomatology, including rehabilitation strategies [11, 12]. Even though a recent review reports the absence of statistical significance on the effect of multidisciplinary treatment over conventional treatment [13], a large body of scientific literature seems to converge on the usefulness of multidisciplinary rehabilitation for managing PD. In particular, this type of treatment has been shown effective on measures of Quality of Life [14], measures of motor symptoms [15, 16], non-motor symptoms as cognition, anxiety, and depression [17] and functional measures [18]. Moreover, it is also true that the nature of multidisciplinary treatments differs highly between studies: they can be composed of physiotherapy and cognitive training [19], physiotherapy and occupational therapy [20] or performed by multidisciplinary teams [21]. This heterogeneity points to the need for new standardized and highly controlled studies on this topic.

A recent phase 2 clinical trial in de novo PD patients compared moderate (60%-65% maximum heart rate), high-intense (80%-85% maximum heart rate) endurance exercise and usual care 4 days per week for 6 months. The clinical outcome was 6-month change in UPDRS Part III. Compared to usual care, high-intensity treadmill exercise resulted in fewer motor changes. Interestingly, the high-intensity group experienced an increase in maximal aerobic power ($\dot{V}o2\max$) compared with baseline [22].

In a recent single-center, double-blind, randomized controlled trial (Park-in-Shape) the authors aimed to evaluate the effectiveness of aerobic exercise delivered at home on relieving motor symptoms in PD subjects with mild disease severity. According to the authors, patients with mild disease severity can reduce off-state motor symptoms by performing aerobic exercise at home [23].

Non-pharmacologic treatment has not only been shown to affect symptomatology, but there is also preliminary evidence in favor of an effect of physical exercise on brain plasticity [24–26]. In particular, the effects of exercise could affect several plasticity-related aspects, among which synaptogenesis, angiogenesis, and neurogenesis [27, 28]. Results on animal models reveal that physical exercise causes changes in neurotrophic factors (NFs) [29–31]. On the same line, there are few studies in the literature linking the benefits of aerobic exercise in PwPD to the involvement of plasticity processes, such as increases in serum brain-derived neurotrophic factor (BDNF) [32] and BDNF-tyrosine receptor kinase B (TrkB) levels [33]. However, the paucity of studies in the literature and their methodological pitfalls do not allow solid conclusions on a potential increase of NFs levels in PD [26].

The absence of methodologically solid studies on the effect of multidisciplinary interventions and their effect on biomarkers points to the need for new standardized controlled randomized clinical trials on this topic.

Moreover, there is still a high level of heterogeneity among studies regarding the detection of α-synuclein as a main biomarker in PD patients [34]. For this reason, in addition to α-synuclein, we have included as a co-primary outcome a set of biological markers closely interconnected with α-synuclein in the PD pathological processes.

Our main research question was whether an integrated motor-cognitive aerobic rehabilitation approaches could affect the biological mechanisms underlying neurodegenerative processes in PD. Coherently, we decided to investigate the modifications of a new set of fluid-based PD biomarkers in response to an intensive rehabilitation program by a single-blind randomized controlled trial.

### Study objectives

The study aims to investigate the effect of an intensive, multidisciplinary, outpatient treatment protocol on a set of molecular biomarkers as well as on balance, gait, aerobic performance, cognitive functions, motor and non-motor symptoms in PwPD.

## Materials and methods

### Study design

The present study is designed as a randomized, controlled, two-arm trial with 1:1 allocation. It is a non-pharmacologically interventional study, and it compares a 6-consecutive weeks of daily outpatient intensive multidisciplinary rehabilitation treatment (Experimental Group, EXP-Group) to a 6-consecutive weeks of daily home-based self-treatment stretching program (Control Group, CTRL-Group) in PwPD.

A SPIRIT schedule of enrolment, interventions, and assessments can be found in Fig 1.

**Fig 1 pone.0309405.g001:**
[figure not shown]
SPIRIT schedule of enrolment, interventions, and assessments.

This protocol was constructed following the Standard Protocol Items: Recommendations for Interventional Trials (SPIRIT) checklist (see S1 Checklist) [35].

Participants conforming to the inclusion criteria are randomly allocated to the EXP-Group or to the CTRL-Group. Each participant then undergoes multidimensional in-depth assessment before (T1), at the end of treatment (T2) and 3 months after the end of treatment (T3). Fig 2 outlines the participant timeline (time schedule of enrolment, interventions and assessments).

**Fig 2 pone.0309405.g002:**
[figure not shown]
Participant timeline (time schedule of enrolment, interventions, and assessments).

### Study setting

The study takes place at the Center for Diagnosis and Rehabilitation of Parkinson’s Disease and Parkinsonisms (DiaRiaPARK) of the IRCCS Fondazione Don Carlo Gnocchi ONLUS in Milan. PwPD allocated in EXP-Group carry out the rehabilitation program within the setting called Complex Outpatient Macroactivity (i.e. Macroattività Ambulatoriale Complessa, “MAC”) while the participants allocated to the control group carry out the self-treatment program at home. All assessments for each time point are performed in the clinic.

### Subject recruitment

Participants are consecutively recruited at the DiaRiaPARK. Recruitment of participants started on December 9, 2020, and is anticipated to be completed by December 31, 2024. Once the subjects are selected, they receive a detailed explanation of the research procedures, and the subjects voluntarily express their consent to participate in this study, signing the informed consent.

### Sample size

There are currently no clinical studies examining the effectiveness of rehabilitation treatment on our primary outcomes. Therefore, the sample size was determined based on the preliminary results of a recent cross-sectional study by Agliardi and colleagues [36]. In Agliardi’s study a total of 32 PD patients were consecutively recruited and screened and a total of 40 healthy subjects were included as controls using frequency matching for age and gender. The main objective of this study was to identify differences in NDEs derived oligomeric α-Synuclein concentration between PD and healthy controls subjects. Hence, considering 2 degrees of freedom with 80% power; 0,05 alpha and a drop-out percentage of 20%, we planned a sample size of N = 72 (N for each group = 36) that will be more than adequate to control for a potential participants’ drop out.

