### Data analysis

The analyses will be conducted using SAS software version 9.4 and R software version 4.2.1. We will conduct a descriptive analysis of the two treatment groups, including the mean and standard deviation for normally distributed variables and the median and interquartile range for variables deviating significantly from normality. To assess the treatment effect, we will employ an analysis of covariance (ANCOVA) model [44], incorporating covariates (gender, age, and disease duration) to adjust the estimates. This model will be utilized to evaluate the treatment effect both at the conclusion of the treatment period and at the end of follow-up time. The parametric approach will be applied for primary outcomes, characterized by continuous scales. Concerning secondary outcomes, non-parametric tests (Wilcoxon rank-sum test) will be employed for those assessed with ordinal scales. Estimates of primary outcomes will be adjusted using False Discovery Rate correction [45]. A 95% confidence interval will be employed, and statistical significance will be reported for any observed differences between groups with a significance level set at p < 0.05. Subgroup analyses will be conducted to examine whether the treatment exhibits a differential effect based on the severity of the patient, as determined by baseline values of the Hoehn and Yahr scale or UPDRS III scale.

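### The stated 80% power comes from a one-time PD-versus-healthy contrast and 2 degrees of freedom, so it is not shown to apply to the planned 1-df comparison of two PD arms

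*Protocol article*

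**What the plan says.** The Sample size section first states that no clinical study has examined rehabilitation on the primary outcomes. For that reason "the sample size was determined based on the preliminary results of a recent cross-sectional study". That study had 32 PD patients and 40 healthy subjects, and its main aim was to "identify differences in NDEs derived oligomeric α-Synuclein concentration between PD and healthy controls subjects". The next sentence draws the conclusion: "considering 2 degrees of freedom with 80% power; 0,05 alpha and a drop-out percentage of 20" per cent, "we planned a sample size of N = 72 (N for each group = 36"). No test is named for the 2 degrees of freedom.

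Other sections describe the comparison that the trial will make:

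- **Study design:** two arms, 1:1 allocation, all participants with PD.
- **Outcomes and measurement:** the primary outcome is change in molecular biomarkers. Table 1 lists 14: eight in NDEVs (oligomeric α-synuclein, three SNARE proteins, BDNF, pro-BDNF, GDNF, CDNF), five pro-inflammatory cytokines and IL-10.
- **Data analysis:** an ANCOVA adjusted for gender, age and disease duration, used to "evaluate the treatment effect both at the conclusion of the treatment period and at the end of follow-up time", with a False Discovery Rate correction for the primary outcomes.

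**The concern.** A power figure belongs to one test of one contrast. Here the contrast behind the figure is disease against health, measured once and without treatment. The contrast to be tested is the difference between two treated PD groups after 6 weeks, and again 3 months later. Nothing in the article links the size of the first to the size of the second. The control arm also follows a daily exercise programme.

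The degrees of freedom do not fit either. A two-group treatment effect in an ANCOVA at one time point uses 1 numerator degree of freedom. Two would fit three groups, or a joint group-by-time test over T1, T2 and T3. The Data analysis section describes neither.

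What is at stake is how the results are read. If 80% is taken at face value, a non-significant result may carry more weight against a biological effect than the trial can support.

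**Working it through.** **Inputs from the article.** Power 80%; alpha 0.05 (sidedness not stated; two-sided assumed); dropout 20%; 36 per arm; two arms; 14 primary biomarkers with FDR correction.

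**1. The plan's own figure.** N = 72 cannot be derived forward from the article, because the effect size and SD are not printed there. They may be in the full protocol, so this is no criticism. The dropout step is consistent: 57 / 0.8 = 71.25, which rounds up to 72. In the other direction, 72 × 0.8 = 57.6, or 28.8 evaluable per arm.

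**2. What the planned test can detect.** For a two-sample comparison with n per arm, the noncentrality is d × √(n/2) on 2n − 2 degrees of freedom, with d in SD units. Solving for 80% power at two-sided 0.05:

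| n per arm | detectable d |
|---|---|
| 28.8 (20% dropout) | 0.751 |
| 29 | 0.749 |
| 36 (no dropout) | 0.670 |

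Normal approximation as a check: √(2/29) × (1.960 + 0.842) = 0.736. Allowing for the three covariates hardly changes this: at N = 58 the detectable f is 0.375, so d = 2f is about 0.75.

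**3. Direction of the degrees-of-freedom mismatch.** The noncentrality needed for 80% power at 0.05 (chi-square form) is 7.85 with 1 df and 9.63 with 2 df. The ratio is 9.63 / 7.85 = 1.23, so a 2-df calculation asks for about 23% more patients at the same noncentrality per patient. At noncentrality 9.63, a 1-df test has about 87% power. Taken alone, the mismatch is conservative.

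**4. Sensitivity to the borrowed contrast (illustration).** Assume that the design effect was 0.751 SD. This value is back-solved from N and is not in the article. Assume also no precision gain from baseline, and 28.8 per arm:

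| share of 0.751 SD achieved | d | power |
|---|---|---|
| 100% | 0.751 | 80% |
| 75% | 0.563 | 56% |
| 50% | 0.376 | 29% |
| 25% | 0.188 | 11% |

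If baseline were also in the model and correlated 0.7 with the outcome (assumed), the residual SD would be √(1 − 0.49) = 0.714. Power at half the effect would then rise to about 50% (noncentral t) to 52% (normal approximation) with 29 per arm.

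**5. Effect of the FDR correction.** In a step-up FDR procedure over 14 tests, the strictest step is 0.05 / 14 = 0.00357. At that level and 80% power, the detectable d with 29 per arm is 1.03 (normal approximation: √(2/29) × (2.914 + 0.842) = 0.99), so about 1.0 SD. If several biomarkers respond, the later steps are less strict and the figure lies between 0.75 and 1.0 SD.

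**The case against.** The article is open about the proxy: it says that no treatment data exist and names the kind of study used in their place. It does not say whether the mean gap, part of it, or only the variability was taken from that study. A reader might infer that the plan assumes rehabilitation brings α-synuclein fully to healthy levels relative to control. The text does not support that; it is one possible reading of a calculation that is not shown. For the same reason, the 56%, 29% and 11% are not estimates of this trial's power.

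The 2 degrees of freedom may come from a repeated-measures calculation over three assessments, and the resulting error would be on the safe side. The full 20% dropout may also be pessimistic, since the Discussion expects few dropouts, and adjustment for baseline could sharpen the comparison.

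A reader might also infer that the missing effect size and SD, or the remark on adequacy for dropout, are faults. Neither holds. An article may leave such inputs to the full protocol, and the dropout step reconciles to 72.

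These points limit the finding but do not remove it. Disclosing a proxy does not carry its power over to another contrast, and the Data analysis section describes no 2-df test.

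**Conclusion.** The concern holds in a limited form. The 80% is attached to a contrast and to degrees of freedom that differ from those of the planned analysis, so it is not shown to describe this trial's treatment comparison. The borrowed contrast is what threatens the claim.

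What can be stated without outside data is the detectable difference for one biomarker at one time point: about 0.75 SD after 20% dropout, 0.67 SD with none, and about 1.0 SD at the strictest FDR step after dropout. These figures assume a two-sided 0.05 level before correction and SD units that refer to the residual SD of the fitted model. At 28.8 per arm a true difference of 0.5 SD would have about 46% power before any correction. It would be going too far to say that N = 72 is wrong; the article does not give the inputs to show that.

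**What to change.** Keep N = 72. Remove the 2-df statement and the 80% claim drawn from the case-control difference, and replace them with wording such as:

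> With 36 per arm (about 29 after 20% dropout), a 1-df two-arm comparison of a single biomarker at a given time point has 80% power at two-sided 0.05 for a between-arm difference of about 0.75 residual SD (0.67 with no dropout), before FDR correction over the 14 primary biomarkers. At the strictest FDR step (0.05/14) the detectable difference is about 1.0 SD. No data exist on the expected treatment effect.

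If a joint group-by-time test was in fact intended, the Data analysis section should say so, and the two sections should then be reconciled on that basis.

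The cost is wording only. No patients are added, but the stated figure becomes less favourable.

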### Eligibility criteria

#### Inclusion criteria

Clinical diagnosis of PD by a movement disorder specialist according to MDS Criteria [37], participants aged between 50 and 85 years, modified Hoehn & Yahr (mH&Y) [38] stage from 1.5 to 3 and stable pharmacological treatment in the previous 4 weeks.

#### Exclusion criteria

Vascular, familiar and drug- induced forms of parkinsonism, other known or suspected causes of parkinsonism (e.g., metabolic, brain tumour etc) or any suggestive features of atypical parkinsonism; significant comorbidities and/or severe systemic diseases that would preclude exercise participation (e.g. recent surgery, unstable cardiac dysfunction, anemia, hepatosis, pulmonary disorders, chronic renal failure; auditory, visual and/or vestibular dysfunctions, presence of DBS); previously diagnosed psychiatric diseases; clinical diagnosis of dementia as defined by Montreal Cognitive Assessment (MoCA Test) Correct Score<15.51 [39]; rehabilitation treatment in the previous 4 weeks. If the participant is unable to comply with inclusion criteria or currently participating in another interfering research project or undergoing any interfering therapy, he/she is not be recruited.

### Randomization and blinding

Once recruited, participants are randomly allocated to two different groups, the Experimental (EXP-Group = 36) and the Control Group (CTRL-Group = 36). A sample block randomization method is employed. The random allocation table is generated by computer and stratified based on PD stages according to mH&Y classification (from 1.5 to 3).

The study involves a single-blind procedure; the allocation of subjects to intervention or control groups is blinded to assessors. Participants are blinded to the benefits of each intervention and the study hypothesis.

Blinded assessments are performed at T1, T2, and T3 by a movement disorder specialist.

### Participant engagement

The study’s details and timescales are explicitly discussed with participants before starting the treatment to ensure they are fully aware of the demands of it, as well as the potential impact on fatigue levels. In addition, the study has the added benefit of providing participants with the opportunity to receive a comprehensive evaluation of their clinical status (i.e., neurological, motor, and neuropsychological evaluation), which is rarely offered, as part of routine care.

### Interventions

#### Experimental group

The rehabilitation program lasts 6 consecutive weeks and involves the execution of a total of 30 days, one for each day of the week (from Monday to Friday) in an outpatient setting. Sessions last 160’/day (80’ motor, 40’ cognitive, and 40’ speech therapy rehabilitation) for 3 days a week and 180’/day (80’ motor, 60’ cognitive, and 40’ speech therapy rehabilitation) for 2 days a week.

*Motor rehabilitation*. The motor rehabilitation program is based on relevant literature and clinical guidelines [40]. The total number of physical therapy sessions is 60, each session lasts 40 minutes and 2 sessions are provided per day. A “circuit” training is performed in 18 out of 60 sessions, 3 times per week on alternate days. The “circuit” training comprised the combination of aerobic training on a treadmill and task-oriented balance exercises in the same session, as previously shown in the study conducted by Soke et al. [41]. During the aerobic training, participants walk on a treadmill for 20 minutes while maintaining a Rate of Perceived Exertion (RPE) between 13 and 15 points (moderate-high intensity of the activity). The RPE can be considered as a proxy of a physiological parameter, assessing the intensity of physical activity perceived during the activity itself [42]. The speed and slope gradually increase and adjust to achieve the desired RPE level. In the same session, the remaining 20 minutes are dedicated to improving static and dynamic stability using a task-oriented approach that promotes explicit motor relearning. The approach involves information on the relative position of the center of mass with respect to the base of support, controlling axial segments, and using vestibular, visual, or proprioceptive information based on the subject’s specific impairments.

Due to the high effort required for the “circuit” training, the physical therapist has the freedom to choose exercises for the participants in the remaining 42 sessions of “conventional” training (7 x week). These exercises will be based on the clinical needs of the individuals, following the recommendations provided in the guidelines [40]. Some examples of exercises that may be included are resistance training, dual-task exercises, biofeedback exercises, joint mobilization, and exercises to manage the freezing of gait.

*Cognitive rehabilitation*. Cognitive rehabilitation or enhancement treatment involves an individualized program developed and supervised by a neuropsychologist; such treatment is mainly targeted frontal/executive/attentive/visuo-spatial-constructive functions in addition to memory and language functions. The cognitive treatment is proposed both in traditional mode (40’; 3 times/week) and through the support of a semi-immersive "Virtual Reality Rehabilitation System” (VRRS) [43] (60’; 2 times/week). The VRRS protocol consists of individual cognitive exercises for 6 weeks, 2 times a week for 60 minutes per session (N = 12). Each session is planned with six cognitive exercises lasting 10 minutes, designed to improve executive functions, visuospatial abilities, attention, and memory. A pre- and post- training sessions are conducted to tailor the cognitive intervention to the subjects’ baseline performance and to evaluate the abilities at the end of treatment. At the end of each session, subjects receive feedback on their performances, and a detailed report of the results is available to the therapist, allowing the monitoring of progress over time. Progression is constantly monitored, and the exercises adaptively modulated in difficulty.

*Speech therapy*. Participants undergo an individualized program supervised by a speech therapist that includes assessment and treatment of voice (dysphonia), articulation (dysarthria), and deglutition (dysphagia). Innovative techniques are used for both assessment (acoustic speech analysis) and treatment (biofeedback with Vitalstim) (40’; 5 times/week). In addition, recommendations for proper deglutition are provided, and counselling sessions (e.g., training about the use of ad hoc products for dysphagia) are offered to the patient and caregiver.

